## Abstract

**Background:**

Evidence suggests that the communication of type 2 diabetes (T2D) genetic risk alone has limited effectiveness on facilitating behavioral changes among individuals of European descent. Although the use of wearable devices has been associated with changes in behavior, the effects of combining personalized precision medicine with wearable devices on behaviors related to T2D prevention remain unclear. This study aims to assess the novel effects of T2D genetic risk communication and wearable device functions on objectively measured moderate to vigorous physical activity (MVPA) time among East Asian individuals with overweight or obesity.

**Objective:**

The objectives of this study are to (1) investigate the effects of communicating T2D genetic risk and (2) examine the effects of combining T2D genetic risk communication with wearable device functions such as step goal setting and activity prompts on objectively measured MVPA time among East Asians with overweight or obesity.

**Methods:**

In this parallel-group randomized controlled trial, 355 East Asians with overweight or obesity aged between 40 and 60 years are allocated to 1 of 3 groups: 1 control and 2 intervention groups. Blood samples are used for estimation of T2D genetic risk and tested for metabolic risk markers. T2D genetic risk is estimated based on 113 single nucleotide polymorphisms associated with T2D among East Asians using an established method. All 3 groups receive a Fitbit device. Both intervention groups will receive T2D genetic risk estimates along with lifestyle advice, but one of the intervention groups will receive additional Fitbit functions: step goal setting and prompt functions. The intervention materials are delivered weekly using WhatsApp and monthly via email. The primary outcome is MVPA time, which is objectively measured with the built-in accelerometer of the Fitbit Inspire 3 and will be assessed at baseline, immediately after the intervention, 12 months after the intervention, and at 6-month follow-up. Secondary outcomes include other parameters, such as sedentary time, BMI, systolic and diastolic blood pressure, 5 metabolic risk markers, handgrip strength, sleep, activity calories, self-reported physical activity, self-reported fruit and vegetable consumption, smoking status, and psychological variables.

**Results:**

This study was funded in January 2023. Data collection for baseline assessments began in February 2023. Formal data analysis started in April 2025 after the 6-month follow-up assessments were completed.

**Conclusions:**

To the best of our knowledge, this study will be the first randomized controlled trial to combine T2D genetic risk communication with wearable device functions in any population. Novel findings will be used to inform future lifestyle modification strategies for T2D. We plan to provide a comprehensive report on this study by publishing this analysis plan before the completion of data collection.

**Trial Registration:**

ClinicalTrials.gov NCT05524909; https://www.clinicaltrials.gov/study/NCT05524909

**International Registered Report Identifier (IRRID):**

DERR1-10.2196/65012

## Introduction

### Trial Background and Rationale

Currently, approximately 500 million individuals worldwide live with diabetes, of whom 90% have type 2 diabetes (T2D) [1]. By 2045, the number of patients with diabetes is projected to reach 170 million in China alone [2,3]. Therefore, developing strategies to address the increasing prevalence of T2D cases remains a key public health priority across East Asian countries.

Compared to White populations, East Asian populations have a higher risk for diabetes despite having lower mean BMI levels. An early study conducted among Hong Kong Chinese adults demonstrated that diabetes risk increased at a BMI of approximately 23 kg/m^2^, which did not conform to BMI cutoff values applied to White populations [4]. Subsequent findings from 2 Asian American cohort studies further supported the notion that individuals of East Asian descent have an elevated risk for T2D, as they have greater adiposity than their White counterparts within each BMI category [5,6]. Epidemiological evidence from Hong Kong also revealed that individuals aged between 40 and 60 years accounted for 40% of incident T2D cases [7] and that increased hazard ratios for cardiovascular diseases, cancer, and all-cause mortality were observed among middle-aged adults with prediabetes [8]. Therefore, it is crucial to develop interventions specifically targeting East Asian middle-aged adults with overweight or obesity, given their higher susceptibility to T2D.

Being overweight or obese is a major risk factor for T2D and is typically characterized by prolonged sedentary time and chronic physical inactivity. New exercise guidelines have since been established to promote reductions in sedentary behavior and increases in moderate to vigorous physical activity (MVPA) [9]. Evidence from recent observational and isotemporal substitution studies has demonstrated the benefits of increased accelerometer-derived MVPA time on T2D, ranging from lowered incidence of T2D-related vascular complications to improved insulin sensitivity and glycemic control [10-13]. Taken together, these findings highlight the key role of MVPA in improving health among individuals with overweight or obesity who are at risk for T2D.

The defining characteristic of T2D is the decline in pancreatic beta cell functions, caused primarily by chronic insulin resistance. Although research has uncovered a plethora of risk factors implicated in T2D progression, such as age, diet, physical inactivity, alcohol consumption, BMI, and family history [14], the multifactorial nature of T2D makes it challenging for any single approach to accurately screen for and predict disease risk among individuals at risk.

Owing to advances in genomics and precision medicine, technologies for assessing genetic predisposition to noncommunicable diseases have become increasingly accessible. Coupled with recent genome-wide association studies, these advances have enabled the discovery of genetic variants that exhibit significant associations with T2D among East Asian populations. Accurate genomic sequencing can facilitate genetic risk communication for T2D on an unprecedented scale. This could provide researchers with potential insights into the impact of T2D genetic risk communication on behavioral changes among East Asians.

However, evidence from multiple studies has indicated that communication of genetic risk has limited impact on behavioral changes [15], raising concerns regarding the overall effectiveness of this approach. Nonetheless, these studies share several limitations: (1) genetic risk was communicated without considering behavioral change theories; (2) MVPA, when used as a primary outcome, was often measured through self-report-based measures; (3) genetic risk for polygenic diseases was calculated using singular genetic variants; and (4) most of the studies focused on individuals of European descent, limiting the generalizability of the findings to East Asian populations.

Considering the steady growth of the wearable device market, consumer-based physical activity (PA) trackers have shown promise in serving as a low-cost platform for intervention studies.

Contemporary wearable devices often feature streamlined interfaces and burnished designs and encourage PA behaviors through goal setting and self-monitoring. For researchers, wearables provide objective measurements of lifestyle behaviors while retaining mass appeal for smooth implementation. Previous randomized controlled trials and systematic reviews have shown that interventions incorporating a goal-setting function (eg, at least 10,000 steps per day) in wearables showed high efficacy in decreasing BMI and supporting long-term weight management among participants with overweight or obesity [16-18]. A recent meta-analysis reported that using wearables as a key intervention modality led to an average increase of 1800 daily step counts, 40 minutes of walking time, and 6 minutes of MVPA time [19]. However, communication of genetic information was not included in the intervention, and the interplay between wearable device functions and T2D genetic risk communication remains unclear.

Herein, we present the detailed data analysis plan for, to the best of our knowledge, the first East Asian–focused randomized controlled trial using wearable device functions in conjunction with genetic risk communication to facilitate changes in MVPA. The wearable device (Fitbit Inspire 3) used in the trial includes a built-in accelerometer, enabling the collection of objectively measured PA data. Fitbit functions such as activity goal setting and activity prompts will play a central role in promoting and sustaining MVPA. By combining personalized precision medicine with wearable device functions, the trial aims to provide novel insights into lifestyle modification strategies.

### Trial Objectives and Hypothesis

The main objectives of this trial are to (1) investigate the impact of T2D genetic risk communication and (2) examine the effects of combining T2D genetic risk communication with theory-based wearable device functions (eg, step goal setting and activity prompts commonly found in consumer-grade wearables) on wearable device–measured MVPA time among East Asian middle-aged adults with overweight or obesity.

We hypothesize that T2D genetic risk communication alone will result in minimal increases in objectively measured MVPA time, whereas combining T2D genetic risk communication with wearable device functions will significantly increase MVPA time not only at the 12-month postintervention time point but also at the 6-month follow-up.

## Methods

### Recruitment

Participants were recruited across various communities in Hong Kong primarily via flyer distribution, local minibus advertisements, emails, and word of mouth. Recruitment materials included the study title, research question, brief study information (eg, study period, duration, and key particulars), participant incentives, inclusion and exclusion criteria, sign-up methods, and contact information for the research team.

Flyers were distributed alongside pull-up banners within local communities, and minibus advertisements were placed on the back of local minibus seats. Recruitment emails were circulated within local organizations and community centers. In brief, flyer distribution (183/355, 51.5%) and minibus advertisements (142/355, 40%) accounted for most of the recruited participants, while emails (19/355, 5.4%) and word of mouth (11/355, 3.1%) accounted for the remainder. Interested individuals were asked to complete an online screening form when signing up.

### Trial Design

#### Overview

Figure 1 shows the timeline and protocol of the study. This parallel-group randomized controlled trial commenced on May 11, 2023, and aims to involve 355 participants. Each participant is randomly allocated to 1 of 3 groups: 1 control group and 2 intervention groups (intervention arm 1 and intervention arm 2). The inclusion of 2 intervention arms allows examination of the effects of T2D genetic risk communication alone as well as the combined effects of T2D genetic risk communication and wearable device functions. All participants are asked to wear a Fitbit device throughout the study period for measuring outcome data.

Participants in intervention arm 1 receive a Fitbit device, T2D genetic risk estimates, and a digital lifestyle leaflet. Participants in intervention arm 2 also receive these materials and have their Fitbit devices calibrated such that their daily step goal is 10% higher than their baseline step count. In addition, they receive activity prompts through the Fitbit device. The control group receives only a Fitbit device. The daily step goals for participants in intervention arm 2 are set 10% above baseline based on relative efficiency and higher feasibility. Chapman et al [20] reported that implementing a 50% increase in baseline step count did not result in greater walking activity compared to a 10% increase. Moreover, only 5% of participants did not meet their step goals when given a 10% step goal increase over baseline compared to 16% who were given a 50% increase [20]. On the basis of these findings, implementing a 10% increase over baseline was considered more feasible and effective for motivating participant behavior.

This trial has been registered at ClinicalTrials.gov (NCT05524909).

**Figure 1 figure1:**
[figure not shown]
Overall study timeline and protocol for genetic risk communication and wearable device interventions. CVD: cardiovascular disease; PA: physical activity; T2D: type 2 diabetes.

#### Inclusion Criteria

Eligibility criteria for participants were (1) being aged between 40 and 60 years, (2) being of East Asian ancestry, (3) having a BMI ≥23 kg/m^2^ (according to the World Health Organization BMI cutoffs for Asians), (4) being able to comprehend English or Chinese, and (5) owning a smartphone.

#### Exclusion Criteria

Participants were excluded if they (1) were unable to perform routine daily PAs (as determined by the Physical Activity Readiness Questionnaire), (2) had prior experience with consumer-directed genetic testing, (3) had been diagnosed with any type of diabetes, or (4) were participating in any exercise-related intervention study.

### Intervention

T2D genetic risk estimates, together with a digital lifestyle leaflet, are delivered weekly via WhatsApp (Meta) and monthly via email, as results from prior studies suggest that genetic risk information can promote optimal health behavior changes when communicated at regular and repeated intervals [21,22]. A total of 113 single nucleotide polymorphisms (SNPs), with corresponding odds ratios and allele frequency values for T2D genetic risk, were derived from a genome-wide association study that identified SNPs associated with T2D risk among East Asians [23]. The estimation procedure has been illustrated in our published protocol and supplementary materials of our previous report [24,25]. Participants would then receive their estimated 10-year and remaining lifetime genetic risk for developing T2D, as well as a dichotomized genetic risk category in comparison to the average population risk for T2D (according to the participant’s age and sex): “increased genetic risk” and “no increased genetic risk.” The digital leaflet contains detailed information on the definition and health impacts of T2D, as well as lifestyle advice on 4 major T2D risk factors (ie, PA, diet, weight management, and smoking) as recommended by the World Health Organization.

Participants in intervention arm 2 receive two unique Fitbit features—(1) step goal setting and (2) activity prompts—in addition to the T2D genetic risk estimates and digital leaflet. Each participant’s step goal is set by staff to be 10% higher than their baseline step count, calculated as the average of the 7-day preintervention Fitbit data. The “Reminder to move” function is used as a prompt to interrupt prolonged sedentary periods. When the wearer has not accumulated more than 250 steps within an hour, the device vibrates and displays a reminder message. We have specified an operation period for this function, and the device reminds participants 10 minutes before each hour between 9 AM and 10 PM. All Fitbit functions unique to this intervention can be accessed and modified only by researchers via the Fitbit online dashboard system.

### Randomization

A block randomization approach has been adopted. The randomization list was generated using a computer program by a staff member who had no prior knowledge of participant information. Each block consisted of 6 allocations, with 2 participants assigned to each of the 3 groups per block.

Group allocation has been concealed from study staff until the 7-day preintervention period, during which staff would have prepared the corresponding intervention materials for participants. The participants will be initially blinded to group assignment; however, blinding will not be possible once the intervention is delivered. A statistician blinded to group assignment will perform outcome analyses using deidentified data.

### Sample Size

To ensure sufficient statistical power, we intend to recruit 355 East Asian participants with overweight or obesity. An oversampling strategy has been adopted, with 35.1% (87/248) of the full sample consisting of individuals at a higher genetic risk for T2D. The required number of participants (n=87) for subsample analysis was based on the desired medium effect size (*F*=0.3085), derived from a 3-group comparison. The control group’s average wearable device–measured MVPA time was 80 (SD 35) min/d. The intervention group receiving genetic risk information alone (intervention arm 1) demonstrated minimal changes (85 min/d), while the intervention group receiving combined genetic risk information and wearable device functions (intervention arm 2) was expected to show a difference of approximately 23% in MVPA time (105 min/d; [(105 − 85) / 85 × 100%], corresponding to a difference of 23% in MVPA time compared to previous Fitbit interventions) [26].

Our sample size calculation assumed an α level of 5%, a power of 80%, and a correlation of 0.70 among 3 repeated measures. A total of 355 participants are recruited to ensure the inclusion of an analysis sample of 248, while factoring in an expected attrition rate of 20% (71/355) and an anticipated Fitbit data missing rate of 10.1% (36/355), independent of attrition, considering instances of insufficient battery life or device loss.

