### Framework

We adopt a superiority hypothesis testing framework for this trial, examining whether combining T2D genetic risk communication with theory-based wearable device functions will lead to significant increases in objectively measured MVPA time and whether such changes will be sustained at the 6-month postintervention follow-up. Each intervention group (intervention arm 1 and intervention arm 2) will be compared separately with the control group and with each other.

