### Statistical Principles

We will present 95% CIs with adjusted marginal means to compare differences between groups at each measurement time point (baseline, immediately after the intervention, 12 months after the intervention, and 6-month follow-up). Results for the interaction term will also be presented. Pairwise between-group comparisons will be performed with Bonferroni adjustment. An overall level of statistical significance will be set at α=.05 before adjustment.

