### Analysis Methods

#### Primary Outcome

We will perform primary outcome analysis according to intention-to-treat principles using a series of linear mixed effects models with fixed effects for time, group, and group × time interactions for objectively measured MVPA time, with repeated measures for each participant. Models will be adjusted for potential confounders such as age, sex, and BMI. Adjusted marginal means with 95% CIs will also be presented to compare differences between study groups across all assessment time points.

The analysis will use a longitudinal data analysis model to examine patterns of differences across assessment time points, study groups, and group × time interactions. Results for the group × time interaction term will be included. In addition to the 4 assessment time points, the analysis will also be performed with time as a continuous variable across the study period. The effect modification will also be investigated according to the level of T2D genetic risk, which will be further categorized based on the average T2D genetic risk estimate and educational level of the sample (ie, between college and noncollege graduates). This post hoc categorization can enable us to examine the intervention effects within each group of genetic risk. To ensure fair random assignment of participants between the groups, we will examine between-group differences in the primary outcome data, using an ANOVA test or, if parametric assumptions are not met, a Kruskal-Wallis test.

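### The 80% power quoted for the 87-person subsample belongs to an unadjusted three-group omnibus test, not to the Bonferroni-adjusted pairwise comparisons at each visit that the plan describes

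*SAP article*

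**What the plan says.** **Sample Size.** "The required number of participants (n=87) for subsample analysis was based on the desired medium effect size", an effect size of 0.3085 that was "derived from a 3-group comparison". The inputs are control 80 min/d (SD 35), arm 1 85 min/d and arm 2 105 min/d, with α 5%, power 80% and a correlation of 0.70 among three repeated measures. The 23% difference offered in support of the effect is itself pairwise, 105 against 85. No pairwise power is given.

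**Framework.** Each intervention arm "will be compared separately with the control group and with each other".

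**Statistical Principles.** The plan will present "95% CIs with adjusted marginal means to compare differences between groups at each measurement time point", and results for the interaction term. It adds: "Pairwise between-group comparisons will be performed with Bonferroni adjustment".

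**Analysis Methods, Primary Outcome.** A linear mixed model with group, time and their interaction. "Models will be adjusted for potential confounders such as age, sex, and BMI"; baseline MVPA is not among the variables named. Intervention effects are to be examined within genetic-risk groups, but no testing rule specific to those groups is given.

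**The concern.** The subsample was sized, and higher-risk people were oversampled, so that intervention effects could be examined among them. A reader of Sample Size will naturally take 80% as the chance of detecting the 20 min/d advantage of arm 2 over arm 1 in that group. The calculation behind the 80% differs in three ways from the comparisons described elsewhere in the plan:

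- it tests all three groups jointly rather than in pairs;
- it makes no multiplicity adjustment;
- it averages three measures, whereas the comparisons are shown visit by visit.

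If the real power for that contrast is much lower, a non-significant subsample result could be misread as showing that the device functions add nothing for people at higher genetic risk. Part of the loss would also be avoidable: a difference in marginal means at one visit, with group means left free at baseline, makes no use of the 0.70 correlation that the plan itself assumes.

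**Working it through.** **Inputs.** From Sample Size: means 80, 85 and 105; SD 35; correlation 0.70; three measures; n=87; full analysis sample 248. From Randomization: 1:1:1 allocation, hence about 29 per arm at n=87. From Framework and Statistical Principles: three pairwise comparisons with Bonferroni, taken here as α = 0.05/3 = 0.0167, two-sided.

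**Step 1: reproduce n=87.** The grand mean is 90, so the variance of the group means is (100 + 25 + 225)/3 = 116.67 and f = √116.67/35 = 0.3086, against the stated 0.3085. Averaging three measures with correlation 0.70 multiplies the variance by (1 + 2×0.7)/3 = 0.80. The noncentrality is 87 × 0.3086²/0.80 = 10.36 on 2 and 84 degrees of freedom. Power at α 0.05 is 81.5%. The smallest N reaching 80% is 85, which becomes 87 with equal arms. A within-between interaction test would need only 16, and a single-visit omnibus test 105. Of the tests tried, the averaged omnibus test is the one that gives 87.

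**Step 2: pairwise power at one visit, n=87.** SE = 35 × √factor × √(2/29). Power comes from the noncentral t with 84 degrees of freedom; the critical value is 2.443.

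| Contrast at one visit | Variance factor | SE | Arm 2 vs arm 1 (20) | Arm 2 vs control (25) |
|---|---|---|---|---|
| Difference in marginal means | 1.00 | 9.19 | 39.9% | 61.0% |
| Change (group-by-time) | 2(1 − 0.7) = 0.60 | 7.12 | 64.3% | 85.5% |
| Baseline-adjusted | 1 − 0.7² = 0.51 | 6.56 | 72.6% | 91.1% |

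A simulation of four visits with an estimated compound-symmetric covariance (6,000 runs, 29 per arm) gave 38.9%, 63.9% and 72.4% for the 20 min/d contrast. Arm 1 versus control (5 min/d) has 3% to 5%, but the plan expects minimal change there.

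**Step 3: what would give 80% for arm 2 versus arm 1.** In the same order of contrasts, the total N needed is 198, 120 or 102. The difference detectable with 80% power at n=87 is 30.3, 23.5 or 21.7 min/d.

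**Step 4: sensitivity, arm 2 versus arm 1, same order.**

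- Correlation 0.5: 40%, 40%, 53%. Correlation 0.6: 40%, 50%, 61%. Correlation 0.8: 40%, 84%, 88%.
- Counting visits in the Bonferroni divisor as well (9 or 12 tests): about 23% to 26% for marginal means and 54% to 58% baseline-adjusted.
- Subsample of 124 (an assumed half of 248): 57%, 82%, 89%.
- Keeping the plan's averaging of three measures (factor 0.80) and changing only the test to the Bonferroni-adjusted pairwise one: 50%.
- Change averaged over three post-baseline visits (factor 0.80 + 1 − 2×0.7 = 0.40): 84%.

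**Step 5: full sample of 248, α 0.05/3.** Arm 2 versus arm 1: 89.6%, 99.0%, 99.7%.

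**The case against.** Several points on the other side carry weight.

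- **Sample Size says nothing false.** It states openly that the effect size came from a three-group comparison and claims no pairwise power. This stands; the fault is a mismatch with the comparisons described elsewhere.
- **The pairwise rule is not stated for the subsample.** The plan treats genetic risk as effect modification with a post hoc categorization. This stands, and the figures are conditional on it. Yet the text sits within the primary-outcome analysis and offers no other rule.
- **The mixed model has a group-by-time term.** Contrasts of change use the baseline correlation, so 40% is the least favourable reading. This stands. The plan lists both marginal means and the interaction, which is why 64% is shown beside 40%.
- **The covariate list is open-ended.** Baseline MVPA is not ruled out. True, but it is not specified either, and it matters more to precision here than the choice of test wording.
- **The subsample may not be 87.** The Intervention section uses "a dichotomized genetic risk category in comparison to the average population risk for T2D", while Analysis Methods refers to risk level, "which will be further categorized based on the average T2D genetic risk estimate and educational level of the sample". The two cuts need not select the same people. At 124, the change and baseline-adjusted contrasts pass 80%.

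A reader might infer that 80% is reached for no test except the omnibus one, or that every subsample contrast is underpowered. The numbers do not support that: arm 2 versus control reaches 86% to 91% once baseline is used, and arm 2 versus arm 1 reaches 84% as change averaged over three visits. Nor do they support reading this as a weakness in the trial's main hypotheses, which are tested in 248.

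**Conclusion.** The point holds in a limited form. The 80% at n=87 describes an unadjusted omnibus test on averaged measures and should not be read as the power of the pairwise, Bonferroni-adjusted, per-visit comparisons. If those comparisons are made in a subsample of 87, arm 2 versus arm 1 at a single visit would miss a true 20 min/d difference in about 60% of cases from marginal means, 36% from change contrasts and 27% with baseline adjustment. After baseline is used, this is the only contrast expected to show a material effect that stays below 80%.

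The conclusion assumes 29 per arm, a divisor of 3, two-sided tests, correlation 0.70, no other covariates, the same effect at each post-baseline visit, and a high-risk group of exactly 87. A correlation of 0.8 or a subsample of 124 would remove the shortfall for the change and baseline-adjusted contrasts; a correlation of 0.5 or a larger divisor would deepen it.

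**What to change.** 1. **Analysis Methods.** Take the between-group contrasts at each post-baseline visit from the same mixed model with group means constrained equal at baseline, or with baseline MVPA as a covariate. Randomization justifies this in the full sample. It also holds within genetic-risk groups, because genotype is fixed before allocation. It raises arm 2 versus arm 1 in the subsample from 40% (marginal means) or 64% (change) to 73%, using data already collected.
2. **Sample Size.** State that the 80% refers to the unadjusted omnibus test, and that baseline-adjusted, Bonferroni-adjusted power at one visit in the subsample is about 73% for arm 2 versus arm 1 and 91% for arm 2 versus control, with the assumptions above.

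It would also help to say which risk cut defines the high-risk group, since the power figures depend on its size.

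The cost is one model constraint and two or three sentences. Enrolment, intervention, outcomes and full-sample hypotheses do not change. The Abstract says that formal analysis started in April 2025, whereas the Results section puts it in the future. If it has begun, the baseline-constrained contrasts should be labelled as added after the plan.
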